##### Outcome assessments

To assess the likely size required for a full-scale trial, we need some estimate of the variability of the primary outcome and, in particular for a cluster randomized trial, an estimate of the intracluster correlation coefficient (ICC). Relying on pilot studies or even on single previous trials for reliable estimates of the ICC is problematic because sampling errors are very large. Nevertheless, the randomization units in this study are unusual, and ICCs from a number of other similar studies (the safest way of calculating ICCs) will not be available. Because of this circumstance, we will calculate an ICC from this study using standard analysis of variance techniques, although we will also attempt to triangulate this with other information available if possible.

### Economic costs

Using economic analysis, we will examine the feasibility of a full-scale cost-effectiveness evaluation of the intervention compared to standard treatment from the perspectives of health, social and criminal justice services. A key task of the economic evaluation will be estimating the cost of the nurses’ training in the DIALOG approach plus SFBT-based counseling. We will measure the time taken for training and ongoing supervision and estimate the cost of using the methodological approach set out by Netten and colleagues
[23]. The training costs will be considered in both the short term and the long term, assuming that the training will continue to accrue benefits into the future.

In addition to the costs of the intervention, the services used by participants will be studied. The number of contacts with nurses will be collected from files. The Secure Facilities Service Use Schedule (SF-SUS)
[24] will be used to collect data on all other service use over the 12 months of follow-up. The SF-SUS is completed with information taken from patient files and records on accommodation, health and social care contacts, contacts with criminal justice professionals and daily activities, including education and therapeutic and physical activities, both within the secure facility and in external services. The schedule could thus also be used to collect patient information for those in the study who may be discharged at follow-up. The SF-SUS has been piloted, tested and successfully applied in previous research in secure facilities
[25,26].

The cost per night in each of the units will be calculated using local data wherever possible. Costs accrued outside the facility will be calculated using existing unit cost estimates
[23,27]. Resource use differences between the intervention and control groups will not be compared statistically to avoid problems associated with multiple testing. Instead, resource use patterns will be described without statistical comparisons. Total costs will be calculated as the costs of time in the units, any external costs and, for the intervention group, the cost of training the nurses in the DIALOG approach plus SFBT.

Costs and outcomes will be combined in a cost–consequences analysis whereby costs are reported alongside a range of outputs
[27]. The cost-effectiveness of the intervention compared to standard care will be assessed using primary (quality of life) and secondary (disturbance) effectiveness outcomes. Incremental cost-effectiveness ratios (ICERs) will be estimated as a cost per 1-point improvement in the patient’s MANSA satisfaction scale score for the primary outcome and as a cost per incident avoided (for example, violent act, suicide attempt, escape) for secondary outcomes. The small number of clusters and participants in this pilot study does not permit an assessment of uncertainty around the ICER point estimates using probabilistic methods, nor does it allow for adjustments for the cluster randomized design. Nevertheless, we will identify the major sources of uncertainty and estimate the impact of this uncertainty on ICERs in deterministic sensitivity analyses.

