## Background

The UK Department of Health
[1] defines *forensic mental health care* as the provision of mental health services for people with mental disorders who are offenders or at risk of becoming offenders. Services are provided in secure, community, NHS and criminal justice settings. The patients include difficult, dangerous and/or extremely vulnerable people whose behaviors present a risk to themselves as well as to others. They can be difficult to engage in assessment, treatment and research, and staff must meet the therapeutic needs of patients while addressing legal, security and public safety issues.

The increasing importance of forensic mental health care can be shown by an increase in medium-secure unit beds in NHS Trusts in England and Wales from 2,500 in 1997 to 3,723 in July 2007
[2]. The average cost of a medium-secure unit bed in London in 2006 was approximately £460 per day
[3]. These figures indicate that the annual cost of NHS medium-secure unit places in England is over £500 million. In addition, many prisoners with severe mental illness requiring NHS inpatient care are unable to be transferred, with the principal problem being a shortage of secure psychiatric beds
[4].

Developing a valid therapeutic approach has the potential for producing clinical and economic benefits. The *Best Practice Guidance on Specification for Adult Medium-Secure Services*[5] states that the key security factor within a forensic healthcare setting is relational security: the formation of a therapeutic alliance between staff and patients, with individual patient care at the center of relational security. It also recommends developing patient involvement in all aspects of the service. This publication followed earlier guidance that the interests of patients should lead service developments and that treatment should be guided by their aspirations and experiences
[6]. However, a review of forensic mental health services noted a lack of a patient perspective and involvement in the service

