## Methods and design

### Design

A pragmatic cluster randomized trial has been designed, avoiding any potential contamination between the intervention and control groups in clinical practice. Six medium-secure units will be randomized. Far fewer women than men are resident in secure units. To enable the study to examine the intervention with both men and women in the forensic mental health service, the units are stratified. The first stratum includes four medium-secure units with two male wards in each unit participating in the study. The second stratum consists of two medium-secure units, with one male ward and one female ward in each unit participating in the study. Within both groups, there is a balanced design, resulting in the same number of units in each of the intervention and control groups (Figure 
1). A randomization schedule has been drawn up by a statistician independent of the study. The study will include a population of inpatients in the six forensic medium-secure wards. A 6-month intervention approach is being used based on the work of Priebe *et al*.
[13,14].

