### Participants

The participants are registered mental health nurses and inpatients at six medium-secure units in southern England and London. Nurses will initially be approached in two wards in each of the participating units (12 wards overall). The inclusion criterion for the clinicians will be that they are registered mental health nurses working with inpatients within those wards. Each patient residing in the participating wards is eligible to participate as long as the following inclusion criteria are met: They must have a history of least 3 months of current inpatient treatment in the service and are capable of giving informed consent. There is no time frame for the recruitment of participants. Recruitment will take place until a sufficient number of nurses and patients have agreed to participate. If there are insufficient numbers of participants from the two identified wards, discussions will be held with the clinicians and management teams of the unit to consider whether other wards are able to be included. Informed consent from both nurses and patients is obtained before they are included in the study. To avoid bias, the allocation of a unit into either the intervention or control arm of the study is undertaken only following the identification and recruitment of a sufficient number of nurses and patients from each unit
[16]. The researchers are therefore blinded to allocation status at the point of nurse and patient entry into the study. The allocation is performed by the randomization service of the registered Pragmatic Clinical Trials Unit (PCTU) at Barts and The London School of Medicine and Dentistry.

Pilot studies are limited in terms of the number of participants involved, and it is acknowledged there may be some nurses and patients who leave the study during the 12-month period from baseline assessment to 6-month postintervention assessments. This may occur for various reasons, such as a nurse moving to a different job or a patient moving to another nonsecure unit as treatment progresses. Attempts will be made to follow up all patients who drop out of the study, unless the patient requests to withdraw from the study.

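### Pricing bed-nights at each unit's own local cost confounds unit price with arm in a three-versus-three comparison, and the price gap can exceed the cost of the intervention

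*Protocol article*

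**What the plan says.** All references are to the protocol article.

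- **Price of a night** (Economic costs): "The cost per night in each of the units will be calculated using local data wherever possible".
- **Price of other services** (Economic costs): "Costs accrued outside the facility will be calculated using existing unit cost estimates". Only the inpatient component is tied to the individual unit.
- **Total cost** (Economic costs): "Total costs will be calculated as the costs of time in the units, any external costs and, for the intervention group, the cost of training" of the nurses.
- **Use of the total** (Economic costs): incremental cost-effectiveness ratios (ICERs) "will be estimated as a cost per 1-point improvement" on the MANSA, and also per incident avoided. The section says the small numbers permit neither probabilistic uncertainty around the ICERs nor adjustment for the cluster design. It promises deterministic sensitivity analyses of the main sources of uncertainty, without listing them.
- **Randomisation** (Design): "Six medium-secure units will be randomized", and "Within both groups, there is a balanced design, resulting in the same number of units in each of the intervention and control groups". The strata are defined by the male and female ward mix. The later pairing of units (Primary outcome measures) concerns the timing of assessments.
- **Location** (Participants): "six medium-secure units in southern England and London".
- **The only bed price given** (Background): "The average cost of a medium-secure unit bed in London in 2006 was approximately £460 per day".

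**The concern.** Cost per night belongs to the randomised unit. It is the same for every patient in the unit and is not something the intervention acts on. With three units per arm, and neither stratification nor pairing on price, the two arms will have different mean prices by chance. Multiplied by up to a year of nights, that difference goes into the incremental cost.

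Suppose both arms used exactly the same nights and services. The incremental cost ought then to equal the cost of delivering the intervention. Under unit-specific pricing it equals that cost plus the price gap times the nights, and can be several times larger or negative. Both ICERs inherit this, and their point estimates would be reported without a cluster-adjusted measure of error. Estimating cost is one of the pilot's stated objectives, so an avoidable artefact in the base case deserves attention.

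**Working it through.** **1. The protocol's own figure.** The Background puts the annual cost of medium-secure places at over £500 million. Its inputs give 3,723 beds × £460 × 365 = £625 million, which is consistent. This is an order-of-magnitude check only: the bed count covers England and Wales and the price is for London. The protocol states no incremental cost or ICER to reproduce.

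**2. Cost of a bed-year.** £460 × 365 = £167,900 per patient.

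**3. Cost of the intervention.** Ten nurses per ward (Participants), two wards in each of three intervention units, and three training days (Interventions) give 10 × 6 × 3 = 180 nurse-days, or 180/48 = 3.75 per patient. The documents give no day rate. At an assumed £100 to £500 a day, training costs £375 to £1,875 per patient. Assume also one hour of supervision per nurse per month for six months and a 7.5-hour day: 60 × 6 = 360 hours, or £100 to £500 per patient. The total is £475 to £2,375, about 1 to 5 bed-nights.

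**4. Error from price alone.** Assume equal unit sizes, 365 nights for everyone and no effect of the intervention. Then

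SE of arm difference = CV × £460 × √(1/3 + 1/3) × 365.

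The between-unit CV is not in the documents, so a range is shown.

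| Assumed CV | SD per night | SE of arm gap per night | SE per patient-year | In bed-nights |
|---|---|---|---|---|
| 1% | £4.60 | £3.76 | £1,371 | 3.0 |
| 2% | £9.20 | £7.51 | £2,742 | 6.0 |
| 5% | £23.00 | £18.78 | £6,854 | 14.9 |
| 10% | £46.00 | £37.56 | £13,709 | 29.8 |

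The SE equals the intervention cost at a CV of £475/(£167,900 × 0.8165) = 0.35% for the low cost and £2,375/(£167,900 × 0.8165) = 1.7% for the high cost. At a CV of 5% it is 2.9 times the high cost (6,854/2,375). At 1% it is 0.6 times the high cost (1,371/2,375).

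**5. Illustration over the actual design.** There are C(4,2) × C(2,1) = 12 possible allocations. Take invented prices of £414, £445, £475 and £506 in the four-unit stratum and £430 and £490 in the other (mean £460, CV 7.8%). With no effect and identical nights, the incremental cost runs from −£22,143 to +£22,143 per patient; the extreme is (1,471 − 1,289)/3 × 365. Ten of the 12 allocations are at least £7,300 in size.

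**6. How much of the total error is price?** A simulation (20,000 runs, 16 patients per unit) let an assumed share of patients leave at a uniform time in the year, with no cost counted after leaving.

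| Assumed share leaving | SD of incremental cost, common price | Price share of variance at CV 2% / 5% / 10% |
|---|---|---|
| 0% | £0 | 100% / 100% / 100% |
| 10% | about £6,000 | 16% / 54% / 82% |
| 20% | about £8,200 | 8% / 37% / 69% |
| 30% | about £9,500 | 6% / 28% / 60% |

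At 20% leaving and a CV of 5%, the SD is about £10,300 with local prices and £8,200 with a common price. If the true incremental cost is £1,000, the probability of the wrong sign is Φ(−1,000/10,300) = 0.46 and Φ(−1,000/8,200) = 0.45 respectively.

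**The case against.** Local prices reflect what each unit actually spends, and choosing them is a legitimate costing convention. The economic work is framed as testing the feasibility of a later evaluation. Its key task, costing the training, does not depend on bed prices. No progression rule rests on the ICER. Over all possible allocations, own-unit pricing adds variance, not bias. If bed price turns out to be a major source of uncertainty, the promised deterministic sensitivity analyses should pick it up, and an article may leave their list to a fuller plan.

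Most of this stands, and it limits the severity. It does not answer the point about the base case: only one allocation is realised, and its price gap is an error that can be removed at almost no cost.

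A reader might go further in four ways that the documents do not support:

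- **That the ICER mostly reflects which units went to which arm.** This depends on the price spread and on how many patients leave within 12 months, and neither is given. The Participants section expects moves to non-secure units, so the case where nobody leaves is not the natural one. At CVs of 2% to 5% with 10% to 30% leaving, price is 6% to 54% of the chance variance.
- **That no uncertainty will be attached to the ICER.** Probabilistic methods are ruled out, but deterministic sensitivity analyses are promised.
- **That a common price would make the ICER reliable.** Step 6 shows that chance variation in bed-nights remains and that the risk of a wrong sign barely moves.
- **That allowing non-local data where local data are lacking is a separate defect.** It is an ordinary caveat.

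**Conclusion.** The point holds in a limited form. Unit price is confounded with arm in the realised comparison, and nothing stated in the design or the analysis balances or removes it. At £460 a night the resulting error exceeds the cost of training and supervision once the between-unit CV passes about 0.35% to 1.7%, and it is about £6,900 per patient-year at 5%. These figures rest on assumed CVs, assumed nurse day rates and supervision time, equal unit sizes and a full year of nights. Whether price is the larger or smaller part of the total error cannot be determined from the documents. Severity is minor to moderate: this is a secondary, feasibility-stage economic analysis with no decision tied to the ICER.

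**What to change.** In the Economic costs section, state that the base case values nights in both arms at one common cost per night, for example the mean of the six units' costs. Name unit-specific local prices as one of the deterministic sensitivity analyses already planned. Report bed-nights by unit and arm, so that differences in use can be seen apart from differences in price.

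The price contribution to the arm difference then becomes exactly zero in the base case. Chance differences in length of stay remain, so the ICER should still be presented as imprecise.

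The cost is about a sentence of text and one descriptive table. The same local prices are collected and only their role changes. The small downside is that base-case totals no longer match each unit's own budget.

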Ten nurses from each ward in the intervention units will be trained in the structured communication approach to allow for some dropouts. The trial will recruit 96 patient participants (48 each in intervention and control arms) to allow for some dropouts. The findings of this study will be used to estimate variability in outcomes for a later, larger study. As this is a pilot study, a formal sample size calculation is inappropriate.

Many complex interventions require a long-term commitment and often necessitate significant effort from participants. Therefore, the process of recruitment, participation and follow-up will be monitored to ensure that the intervention is acceptable and meaningful to patients and clinicians. The monitoring will take place through structured monthly meetings to be held between a research team member and those involved in the intervention and an in-depth exploration of the patients’ experiences through focus group discussions. The loss of participants over the course of a trial will also be carefully monitored with the offer of follow-up interviews to all participants who either withdraw or drop out of the study, and reasons for leaving the study will be explored with those participants. A nominal sum of £35 will be given to each patient participant upon completion of each set of assessments.

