### Assessment

#### Feasibility

To establish the feasibility of a full-scale cluster randomized trial, we will calculate the estimated treatment effects and corresponding confidence intervals for all outcomes measured at 6 and 12 months. These outcomes are detailed in the following section. We will first calculate a mean value of the outcome for each unit and then calculate the treatment effects (and corresponding confidence intervals) as the mean difference of these means in the intervention and control groups. This is an acceptable method of analyzing data from cluster randomized trials when the number of clusters is small. Given that this is a pilot study, we expect confidence intervals to be wide, and hypothesis testing will be inappropriate. We will instead use the confidence limits of each treatment effect and knowledge of the clinically important difference for each outcome (where this is available) to determine whether clinically important differences are ruled out by these confidence limits. If they are not, then this will indicate that it is worth pursuing a full-scale trial. However, where confidence intervals indicate an unambiguously clinically important effect, we will test the statistical significance using *t*-tests of data aggregated to the cluster level. The aggregation to cluster level will be carried out as already described. We will also consider the recruitment and dropout rates to assess the feasibility of conducting a full-scale trial with similar rates. For the outcomes measured monthly, we will plot data graphically to look at patterns and whether there are any obvious trends. This will facilitate the construction of possible suitable outcome measures for the full-scale trial from these data. In addition, for each outcome measure at each time point, we will examine completion rates, both whether the outcome measure has been completed at all and the extent of completion. This will indicate the feasibility of using the various outcome measures in a full-scale trial and also help to determine the likely size of the trial if we allow for dropouts in a sample size calculation. In addition, the number of participants recruited from each ward, the number of staff and patients who refuse to take part, as well as the number of drop outs will also be recorded. We will be collecting and summarizing data on the attendance of nurses at training events and the timing of the expected monthly sessions between nurses and clients and between nurses and a researcher, to ascertain the fidelity of the intervention. Finally, demographic data collected on each participant at the start of the study will also be used to describe the participants in this study. The research team will reflect on the representativeness of the demographics in terms of the general population of patients that could potentially be use the intervention.

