### Participants’ experiences

#### Evaluation of patients’ experiences

Following the final session, three focus groups will be convened (one in each intervention unit) to draw out respondents’ attitudes, feelings, beliefs and experiences regarding the intervention
[28]. Each group will contain between four and eight patients and last 60 to 90 min. If more than eight patients wish to take part, a further group will be formed. The focus group discussions will be audiotaped and transcribed.

There is strong support for the view that individuals who are similar to the target audience for the project are involved in this process, and one patient member of the research team is involved in developing the interview schedule and moderating the groups
[29]. Training in running focus groups is given by one of the research team members (IM) to ensure competence in focus group techniques
[29]. This approach has been undertaken successfully in a previous project involving members of the project team
[30].

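### The economic section says six units rule out adjusting for the cluster design, which contradicts the protocol's own unit-level method and leaves the incremental cost without a sampling interval

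*Protocol article*

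**What the plan says.** **Design.** The protocol states "Six medium-secure units will be randomized", with a balanced scheme "resulting in the same number of units in each of the intervention and control groups". The section on patients' experiences confirms three intervention units: "three focus groups will be convened (one in each intervention unit").

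**Feasibility section.** For every outcome at 6 and 12 months, which includes MANSA, the plan is: "We will first calculate a mean value of the outcome for each unit and then calculate the treatment effects (and corresponding confidence intervals") from the difference between arms in those means. It adds: "This is an acceptable method of analyzing data from cluster randomized trials when the number of clusters is small". It expects wide intervals and accepts them.

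**Economic costs section.** ICERs are planned as cost per MANSA point gained and cost per incident avoided. The section then says that so few clusters and participants prevent a probabilistic assessment of uncertainty around the ICERs, "nor does it allow for adjustments for the cluster randomized design". Deterministic sensitivity analyses are planned instead. The section does not say how the incremental cost or the incremental MANSA effect is to be calculated.

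**The concern.** The two sections draw opposite conclusions from the same fact. One treats the small number of units as the reason to use a unit-level analysis. The other treats it as the reason why the cluster design cannot be taken into account. Costs can be averaged per unit just as questionnaire scores can, so the reason given in the economic section is wrong on the protocol's own terms.

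Two things follow.

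- **The incremental cost gets no sampling interval.** Deterministic sensitivity analysis varies chosen inputs; it does not show how far the result would move with a different set of units. This matters for cost in particular. The price of a night is to be taken from each unit's local data where possible, so price differences between units are built into the cost of their patients. A chance imbalance in price between three units and three units would enter the incremental cost as if the intervention had caused it.
- **The denominator of the ICER is left open.** If the disclaimer led the analyst to pool patients, the MANSA difference in the ICER could differ from the one in the main results.

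**Working it through.** The protocol gives no power or precision figure to reproduce; it says "As this is a pilot study, a formal sample size calculation is inappropriate". The check is therefore whether the Feasibility method works with these units, and how far the choice of estimator matters.

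**Inputs from the protocol**

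- Six units, equal allocation: 3 per arm.
- "The trial will recruit 96 patient participants (48 each in intervention and control arms) to allow for some dropouts". This gives 96/6 = 48/3 = 16 per unit on average. An equal spread is an assumption.

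**Assumed inputs**

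- ICC from 0 to 0.10. The protocol gives none and will estimate it from the trial.
- Unequal unit sizes of 10, 16 and 22 per arm, for illustration.
- Results are in SD units, because no MANSA SD is given.

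**Step 1: the unit-level interval.** Degrees of freedom are 2 × 3 − 2 = 4, so t = 2.776.

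SE = SD × √[(2/3) × (ICC + (1 − ICC)/16)], and half-width = 2.776 × SE.

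Example at ICC 0.05: (2/3) × (0.05 + 0.95/16) = (2/3) × 0.1094 = 0.0729; the square root is 0.270; the half-width is 2.776 × 0.270 = 0.75 SD.

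For comparison, a patient-level interval that ignores clustering has SE = SD × √(2/48) = 0.204 SD on 94 degrees of freedom, and a half-width of 0.41 SD at any ICC.

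Coverage of nominal 95% intervals was simulated with 10,000 runs per setting and 16 patients in every unit:

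| ICC | SE (SD) | Half-width (SD) | Coverage, unit-level | Coverage, clustering ignored |
|---|---|---|---|---|
| 0 | 0.204 | 0.57 | not simulated | not simulated |
| 0.01 | 0.219 | 0.61 | 95% | 93% |
| 0.05 | 0.270 | 0.75 | 95% | 87% |
| 0.10 | 0.323 | 0.90 | 95% | 78% |

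With sizes 10/16/22, the unit-level interval still covered 95% at each ICC simulated. The unadjusted one covered 93%, 85% and 76%. An adjustment for the cluster design is therefore possible with six units. It is wide, but it holds its level.

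**Step 2: does the choice of MANSA estimator matter?** With 16 in every unit the patient-pooled and unit-level differences are identical. With sizes 10/16/22 they differed by a median of 0.05 to 0.07 SD, with a 95th percentile of 0.14 to 0.20 SD (ICC 0.01 to 0.10).

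Invented unit means show the effect on an ICER. Take intervention units at 4.5, 4.8 and 5.1, every control unit at 4.4, and an incremental cost of 1000:

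- Unit-level difference: (4.5 + 4.8 + 5.1)/3 − 4.4 = 0.40; ICER 2500.
- Pooled, sizes 10/16/22: (45.0 + 76.8 + 112.2)/48 − 4.4 = 0.475; ICER 2105.
- Pooled, sizes 22/16/10: (99.0 + 76.8 + 51.0)/48 − 4.4 = 0.325; ICER 3077.

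**Step 3: an interval for the ratio itself.** By Fieller's method this is bounded only if the interval for the denominator excludes zero. Here the observed MANSA difference would have to exceed roughly 0.6 to 0.9 SD (ICC 0.01 to 0.10). The ratio's interval would often be unbounded.

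No equivalent figure is given for cost, because the protocol does not give the spread of costs within or between units.

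**The case against.** **The clause is about the ICER, not about single outcomes.** It is the second half of a sentence on uncertainty around the ICERs, and step 3 shows that caution about the ratio is fair. That part stands. It does not rescue the clause, which is worded as a general bar on adjusting for the design. Incremental cost and incremental effect are each simple differences that the Feasibility method can handle.

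**The MANSA interval is already planned.** Correct. Readers will see from the main results whether it spans zero. What is missing is the interval for cost, and a statement that the ICER uses that same MANSA difference.

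**A reader might infer that the ICER will rest on a different MANSA effect from the main result.** The protocol does not say so. The economic section names no estimator, the unit-level difference is the natural candidate, and the two coincide when units are equal in size. Divergence is possible, not established.

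**A reader might also count the chance of a wrong-signed ICER against this clause.** If the true benefit were 0.3 SD (an assumption), the estimate would be zero or negative with probability Φ(−0.3/SE) = 0.085, 0.133 and 0.176 at ICC 0.01, 0.05 and 0.10. But that comes from having six units; reporting intervals does not change it. It is a reason to display uncertainty, not a measure of the error.

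**Resource use is deliberately described without statistical comparison.** The reason given is multiple testing, not clustering. It concerns tests of resource-use items and does not bar one interval on total cost.

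**The stakes are low.** This also stands: the economic work is there to judge whether a full evaluation is feasible, and the rule for proceeding to a full trial rests on the confidence limits for the outcomes, not on the ICER.

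**Conclusion.** The contradiction is real and can be seen from the text alone. The economic section's reason for not adjusting for clustering is refuted by the method adopted in the Feasibility section. Followed as written, it leaves the incremental cost without a sampling interval and the ICER with deterministic sensitivity analyses only, and it leaves the effect estimator in the ICER unstated.

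The protocol's method is workable on 4 degrees of freedom. The MANSA half-width of about 0.6 to 0.9 SD rests on 16 patients per unit and an ICC of 0.01 to 0.10, both assumed. The possible gap between estimators rests on assumed unequal unit sizes and vanishes if units are equal.

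The point is worth correcting, but its impact is modest: the analysis is secondary and at feasibility level, and neither the primary analysis nor the sample size depends on it.

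**What to change.** In the Economic costs section:

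1. Delete the clause saying that no adjustment for the cluster design is possible.
2. State that incremental total cost is the difference between arms in unit mean costs, with a t interval (4 degrees of freedom for three units against three).
3. State that the ICER denominator is the unit-level MANSA difference from the Feasibility section.
4. Show both intervals beside any ICER point estimate, and keep the deterministic sensitivity analyses as a supplement.

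The statement that a probabilistic interval for the ICER itself is not feasible may stay. If there is a reason to depart from the Feasibility method, give it instead of items 2 and 3. I would not withhold the ICER whenever the MANSA interval includes zero: that would bring back a significance test in a pilot that otherwise avoids them, and the planned cost–consequences table will be reported in any case.

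The cost is a few lines of analysis on data already to be collected. The downside is that the intervals will be wide, which the Feasibility section already accepts for the other outcomes.
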